In Kristiansand we recruited participants with a variety of educational backgrounds and not only with health background as in Bergen. This was due to recruitment challenges, as finding individuals with such a specific background was practically difficult and would have given us a smaller pool of candidates and thus less statistical power. However, we acknowledge that some baselines characteristic like years of residence or level or integration scores can differ, therefore describing and eventually adjusting for the differences will be crucial. The reason for having Kristiansand as a control group is due to earlier collaboration in the CHART-study. Their Introduction program, at the time of developing the protocol, was one of the few agencies that worked for early integration of refugees in the labor market in Kristiansand.

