### Exclusion criteria

2.8

Participants with physical or mental ailments that require extensive medical follow-up will be excluded from the intervention (e.g., they appear to suffer from deep depression). If participants are already involved in meaningful, health-related work like researching in health care areas, they will also be excluded from the study. Participants with a high level of psychological distress in the intervention group (assessed with Hopkins Symptom Check List with 10 items with mean item score of >1.85) will be referred to a psychologist, who will assess if the participants need further follow-up.

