#### Questionnaire

2.9.1

We have developed a questionnaire that all participants will answer twice: in Bergen, participants will complete the questionnaire once pre- and once post-intervention, and participants in the control arm in Kristiansand will also complete the questionnaire twice but with a six-month period between the responses.

The questionnaire is available in Norwegian and English and includes 40 questions with an expected time to complete of 35 min (Supplementary material A). The following questions, which have been used in several cultural settings, will be included in the survey (32–35).

Sociodemographic, sense of coherence and integration: Background questions on sociodemographic and migration factors are adopted from the CHART-study (26, 27). These questions include information about arrival year, emigration reason, educational level and background, marital status, language level, and household members.

The sense of coherence scale with 13 items (SOC-13) is used to measure subjective sense of comprehensibility, manageability, and meaningfulness in one’s life. SOC-13 assesses how people view their life and identifies how they use their resistance resources to maintain and develop good overall health (36–38). Our questionnaire includes 10 questions from the Immigration Policy Lab Integration Index (IPL-12) related to the domains of integration, linguistic integration, and psychological integration (38). Two questions related to income level and understanding of political matters were excluded as they were not deemed to be necessary.

Variables on health and wellbeing: Self-rated health (SRH) is the individual’s own evaluation and perception of their health and is widely used in research related to health disparities in diverse populations. In our study, self-rated health is the main health outcome, assessed by the question: “How do you currently assess your health?” with the possible answers “very poor,” “poor,” “none,” “good,” or “very good.” Furthermore, the question “Do you suffer from long-term (1-year) illness or injury of a physical or psychological nature that impairs your daily life?” and if yes, “How would you describe the impairment in terms of slight moderate or severe?” is included from the Nord-Trøndelag Health Study-3 (HUNT-3) but is not the main outcome (39).

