### Power calculation and sample size

2.10

This pilot aims to evaluate both the feasibility and effectiveness of the piloted intervention. However, the sample size will probably not be sufficient to rely on statistical significance to address the effectiveness in health outcomes. For reporting the results of the pilot study regarding effectiveness, we will therefore look at trends by using relative risk measures with CI without relying on statistical significance only. If the study is found to be feasible and the trends of effectiveness in a positive direction for the participants, a new study involving a full evaluation of the effect on health as measured by the SRH will require a total sample size of 120 participants with 40 participants in the intervention arm – 20 for each round – and 80 participants in the control arm, based on the assumptions of a 1:2 individually randomized controlled trial with superiority design, with 80% power, 0.05 significance level of assessment, and standard deviation of 1.0 for both arms. The minimum detectable difference between the two arms is calculated to be 0.55.

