### Statistical analysis

2.11

Sociodemographic- and migration-related variables measured at baseline will be described for both the intervention and control arms. Continuous variables will be described with mean, standard deviation, and interquartile range. Categorical variables will be described as counts and percentages (absolute or relative frequency).

We will conduct intention to treat (ITT) analyses. However, it might not always be feasible to obtain information from participants who withdraw from a six-months intervention. As a part of the feasibility exploration, we will try to contact these participants by phone after the intervention period. This will allow us to compare the baselines assessments for those who left the intervention and see if they differ from the rest of the participants.

The effect on health will be measured quantitively regarding changes in self-perceived health for each subject between the intervention and control participants. Based on the questionnaire, SRH scores will be calculated pre- and post-intervention/non-intervention for each participant in both arms. Mean SRH scores will be calculated in both arms and for both time points. Differences in the mean SRH scores at the two time points will be calculated to measure changes in SRH over time. Any difference in SRH change between the two arms will be estimated using both crude (unadjusted) analysis and linear (mixed) regression. We will explore changes in other health and wellbeing assessments in a similar way to determine whether a different measure better detects changes in health. However, we will obtain basic sociodemographic and migration related factors at the baselines questionnaire that will allow us to describe the participants for each of the rounds. In addition, we will collect data on perceived changes in health through qualitative interviews.

Assuming that covariates at baseline are mostly complete, missing outcome values at follow-up due to drop-outs (lost to follow-up) from the study, will be tried corrected for, depending on missingness mechanism, using either simple approaches such as linear regression (Assuming Covariate-Dependent Missing Completely at Random) or more complex approaches [assuming missing at random (MAR)], such as GEE together with multiple imputation or inverse weighting, or using (linear) mixed model approach (using maximum likelihood methods) (49).

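### Section 2.11 sets the SRH effect as a difference in change and never names baseline SRH as a covariate, so the reported trend can rest on one untestable assumption

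*Protocol article*

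**What the plan says.** The protocol article's Questionnaire section (2.9.1) makes SRH the main health outcome ("In our study, self-rated health is the main health outcome, assessed by the question"), a single item with five answer levels. It is measured at both time points in both arms: "We have developed a questionnaire that all participants will answer twice". Section 2.11 then scores it ("SRH scores will be calculated pre- and post-intervention/non-intervention for each participant in both arms"), takes differences ("Differences in the mean SRH scores at the two time points will be calculated to measure changes in SRH over time") and compares the arms: "Any difference in SRH change between the two arms will be estimated using both crude (unadjusted) analysis and linear (mixed) regression". Other health and wellbeing measures are to be explored in a similar way.

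The section on recruitment (2.5) states a general intention to adjust for baseline differences between the cities: "describing and eventually adjusting for the differences will be crucial". Its examples are years of residence and integration scores. No section lists the regression covariates, names baseline SRH among them, or says whether the crude or the regression estimate is the main one.

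Section 2.10 makes a positive direction of the trends, together with feasibility, the condition for a full study. That study is a 1:2 randomised trial of 40 and 80 participants, planned with "80% power, 0.05 significance level of assessment, and standard deviation of 1.0 for both arms" and a minimum detectable difference of 0.55.

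**The concern.** Both the crude analysis and the regression are aimed at the same quantity, the difference in change. Calling the second a mixed model does not bring in adjustment for baseline SRH: with complete data, a standard model with arm, time and arm-by-time terms reproduces the difference in mean change. Unless baseline SRH is a covariate, it enters only by subtraction.

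That matters because the arms differ by design. They are in different cities, health education is required only in Bergen, and the health exclusion is worded for the intervention: "Participants with physical or mental ailments that require extensive medical follow-up will be excluded from the intervention". A baseline gap in SRH is plausible, and its direction is unknown. Screening could make Bergen start higher. The Introduction's argument that stalled accreditation may harm health could make Bergen start lower. Whether the gap is a lasting difference between populations or partly fades by six months cannot be learned from two measurements. A single estimate commits to one answer without showing it, and its direction feeds the decision on a full trial.

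**Working it through.** **Inputs.** From section 2.10: 40 v 80 participants, SD 1.0, 80% power, alpha 0.05 (two-sided reproduces the stated result), difference 0.55. These belong to the later randomised trial. The pilot is to recruit up to 40 and gives no control number, so relative widths carry over to it only at the same 1:2 ratio, and power figures do not carry over. The pre-post correlation rho and the baseline gap are not in the documents and are assumed below.

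**1. The plan's own figure.** SE factor = √(1/40 + 1/80) = 0.1936. Minimum detectable difference = (1.960 + 0.842) × 1.0 × 0.1936 = 0.543 by the normal approximation, or 0.547 by the t distribution. Both round to the stated 0.55 at two decimals once rounded up. Power at 0.55 is 80.4% (t). The figure reproduces.

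**2. Precision with balanced baselines.** With an SRH score SD of 1, the SD of change is √(2(1 − rho)) and the residual SD after adjusting for baseline is √(1 − rho²). The ratio of interval widths is √(2/(1 + rho)).

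| rho | SD change / adjusted | 95% half-width change / adjusted | Change-score interval wider by |
|---|---|---|---|
| 0.3 | 1.183 / 0.954 | 0.449 / 0.362 | 24% |
| 0.5 | 1.000 / 0.866 | 0.380 / 0.329 | 15% |
| 0.7 | 0.775 / 0.714 | 0.294 / 0.271 | 8% |
| 0.8 | 0.632 / 0.600 | 0.240 / 0.228 | 5% |

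**3. Precision with unequal baselines.** A gap of d SDs multiplies the adjusted variance by 1 + d² × (1/3)(2/3).
- d = 0.5: factor 1.056; the change-score interval is 12% wider at rho 0.5 and 6% wider at rho 0.7.
- d = 1.0: factor 1.222; it is 4% wider at rho 0.5, but at rho 0.7 the ratio is 0.98, so the advantage reverses.

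**4. How far the two estimates can differ.** With equal SDs at both times, they differ by (1 − rho) × gap. For a gap of 0.5 this is 0.35, 0.25 and 0.15 at rho 0.3, 0.5 and 0.7. At rho 0.5 that is 0.25/0.55 = 45% of the planning difference. For a gap of 0.3 at rho 0.5 it is 0.15, or 27%.

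**5. Which one is wrong depends on the gap.** A simulation used a five-level item, 40 v 80, no true effect, and an intervention arm starting 0.5 lower on the underlying scale (1,500 runs per setting). Mean estimates:

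| Behaviour of the gap | rho | Change score | Baseline-adjusted |
|---|---|---|---|
| Regresses to the mean | 0.5 | +0.26 | −0.03 |
| Regresses to the mean | 0.7 | +0.16 | −0.03 |
| Stable | 0.5 | 0.00 | −0.28 |
| Stable | 0.7 | 0.00 | −0.18 |

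If the intervention arm started higher, the direction of these errors would be expected to reverse.

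**6. Meaning of SD 1.0.** If it is the SD of change, the stated power stands for a change-score analysis. If it is the SD of the score, the SD of change is at most 1.0 only when rho is 0.5 or more. Power at 0.55 is then 66%, 80% and 95% at rho 0.3, 0.5 and 0.7 for a change score, against 84%, 90% and 98% with baseline SRH as a covariate. Since √(1 − rho²) never exceeds 1, adjustment in a randomised trial keeps the planned power at any rho.

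**The case against.** The strongest reply is that the plan does not rule baseline SRH out. It contrasts the crude analysis with regression, section 2.5 announces adjustment, and section 2.11 refers to baseline covariates when discussing missing data. Regressing change on arm and baseline SRH gives the same arm effect as regressing follow-up on arm and baseline SRH, so the wording could accommodate the adjusted analysis. An article may also leave a covariate list to a fuller document. This stands against a reading that a reader might infer, namely that SRH will be analysed with no adjustment at all; the text does not support that. It does not remove the point that the stated target is change, that a standard mixed model would return the same change contrast, and that neither the role of baseline SRH nor the leading estimate is fixed.

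Second, a reader might infer that the baseline-adjusted estimate is the correct one. The documents do not support that: the arms come from different populations, and with a stable difference the adjusted estimate is the biased one. Nor does linear adjustment remove a ceiling on a five-level item. This objection stands, and is why neither estimate is ranked above the other here.

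Third, section 2.10 speaks of trends in relative risk measures, not mean change, and the article already disclaims power and design to evaluate full effects. Both are fair. But the only between-arm SRH comparison set out in section 2.11 is the difference in change, and the direction of the trend still helps decide whether to go on.

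**Conclusion.** The point holds as a gap in the stated analysis: the effect is fixed as a difference in change, and baseline SRH, though collected in both arms, has no stated role. Under the assumed gap of 0.5 and rho 0.5, either method used alone can produce a false trend of about 0.25 to 0.28, roughly half the 0.55 planning difference, with opposite signs. The size scales with the gap and with 1 − rho, neither of which the documents give.

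The precision gain from adjustment is secondary: 5% to 24% excess width for the change score over rho 0.8 to 0.3 with balanced baselines, less with imbalance, and reversed at a 1.0 SD gap with rho 0.7. It would be wrong to conclude that the change score is always less precise. It would also be wrong to read the power figures as a shortfall of the pilot or as an error in the 0.55: they concern a later randomised trial, and depend on an SD whose meaning section 2.10 leaves open.

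**What to change.** In section 2.11, add a regression of follow-up SRH on arm and baseline SRH. Report it beside the planned difference in change as a pre-specified pair, each with its interval and its assumption (comparability given baseline; parallel trends), without claiming that either is unbiased. Describe the SRH trend as positive only when both estimates agree in direction, and otherwise as dependent on assumptions. Do the same for GHQ-12, HSCL-10 and WHO-5, which are also collected at both times.

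In section 2.10, state whether SD 1.0 refers to the SRH score or to change. If it is the score, say that the later trial will adjust for baseline SRH, which keeps 80% power at 0.55 whatever the correlation. Report the pilot's observed pre-post correlation for that calculation.

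The cost is one extra model per outcome on data already collected. The drawback is two estimates to present, and a less clear-cut trend if they disagree.

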### Evaluation of implementation strategy

2.12

Evaluating an implementation strategy is a complex endeavor for which there is not consensually accepted guidelines (28, 50). Many evaluating components can be included, but in this case, we will focus on feasibility, fidelity, dose received, or satisfaction, and dose of exposure, or participation, as suggested in the guidelines for conducting feasibility and pilot studies for implementation trials (28). In short data on evaluation will be collected through interviews and observations of both participants and mentors following a structured schema for observations and semi-structured interview guides for mentors and participants.

*Feasibility* will be assessed in our study by asking both mentors and participants how they experienced the implementation of the intervention, including the challenges they faced. For mentors, we will ask questions related to the execution of the mentor role. For participants, feasibility will be assessed by asking about the challenges and facilitators related to the placement, both at the personal level and regarding the institutions where they were placed. In addition, feasibility will be assessed through observations at the field.

*Fidelity* will be assessed through observations in the field compared to the study protocol by reviewing our implementation strategy, assessing intervention delivery, and evaluating how the implementation was in line with the purpose of the study and its aims (51).

*Dose received* (satisfaction) is defined as the participants’ satisfaction with the dose of the intervention received and will be assessed through questions to participants regarding the scope of tasks they executed and to which degree they value them in both professional and personal terms (52).

*Dose of exposure* (participation) is defined as the extent to which the participant actively engaged with, interacted with, and was receptive to the intervention. It will be assessed by asking the participants and the mentors about their stay at the institution, the activities they participated in, and their total time spent at the institution.

## Discussion

3

Integration for health (Int4Health) is a research study anchored in the need to address a societal challenge. This protocol is a part of Int4Health aiming to describe how a pilot intervention aiming to improve health through meaningful professional integration, can be implemented. Executing interventions in academia is both complex and multifaceted, with various factors outside of the researcher’s control that can impact delivery of the intervention. Therefore, we must prioritize thorough planning and execution of the intervention. Protocols are also important for transparency, evaluations, and future replications of findings (53). For these reasons, we present in this paper the protocol of a hybrid type 2 study testing an intervention aimed to improve migrant health through meaningful activities.

The possible challenges to the present pilot study must be acknowledged, nonetheless. First, a non-randomized intervention could be vulnerable to unmeasured, confounding variables. Further, differences between the intervention and control arms’ locations and inclusion criteria (e.g., education level) might compromise comparability of the groups. A possible solution for both challenges could have been implementation of a waiting-list design; however, given that our participants already face the issue of waiting for extended periods for work accreditation in their professional field, adding an additional period of waiting was not considered an acceptable alternative.

Next, we acknowledge that the pilot’s small sample size will not have power and design to evaluate full effects on health, and if the pilot is found feasible and experienced positively, it must be later evaluated in a randomized controlled trial design. Recruitment is time-consuming when the inclusion criteria are strict, and the participants must commit to the intervention for at least 6 months. To address this, we have planned two rounds of recruitment and will only include the numbers that our partners believe to be feasible within the pilot period. To further address the small sample size, our methods include both questionnaires and interviews asking participants for their thoughts on how they perceived the intervention’s effect on their health so that we can assess nuances in the intervention’s impact. Reaching out twice 6 months apart to the same control participants in Kristiansand may also pose challenges to data collection, as participants may move, change phone numbers, or avoid contact with the researchers. Though having a control arm is a strength, this arm is unlikely to be a complete match for the intervention arm. Despite these challenges, the control group can still provide us with valuable insights on the development of health in a comparable time period regarding migrants in a compulsory educational setting.

Furthermore, various recruitment challenges may arise before, during, and after recruitment. Loss to follow-up and lack of participants is always a challenge when conducting interventions of this kind. To prepare for a future, full-scale study evaluating the intervention’s effects, we considered that recruiting up to 40 participants for the pilot would give us the necessary information to prepare for larger-scale recruitment. Closely following up on the participants in each round may also strengthen commitment to staying in the program. The observations of the participants on site along with midway evaluation is key to maintain engagement and address challenges that may arise. Therefore, the close relationship between the participants and the first author may function as a buffer against drop-out and is a key strategy for participant retention in both rounds. Given that this is a research study limited in time, we will not have time for long term evaluation of the participants which is a limitation. Nonetheless it would be desirable to contact them 1 or 3 years after the intervention when the project is upscaled.

Accessing the right mentors is also likely to post a significant challenge due to the limited availability of mentors, who will not receive extra resources for participating. Some mentors may also need special accreditation from both the head of their institute and head of administration before allowing anyone into certain workspaces (e.g., laboratory). We intend to use our networks and send information early on to heads of institutes to proactively prevent these problems.

Another challenge is balancing the duration of the intervention. On the one side, 6 months may be too short of a period to detect quantitative changes in health. On the other side, participants may feel that the six-month intervention period is already too long, given that participation is unpaid and does not aid them with the formal accreditation process. However, participation in the study may be a step towards relevant paid employment through gaining a professional network and better understanding of the system.

Lastly, the first author’s combined role as coordinator, administrator, and researcher may be a weakness in this study, as this may contribute to bias, without any blinding. Developing close professional relationships between the first author and participants could also create a certain level of bias in the data, primarily in interviews. Among the measures to counteract this is to thoroughly work on reflexivity, ask colleagues to conduct a portion of the interviews, and include the whole research team in analyzing the anonymized data.

Participation in the intervention is low-risk and we anticipate few adverse effects. Some participants may experience only short-term health and integration improvements. Other participants may experience worsened mental and somatic health after completing the intervention. If this happens, we will guide the participant to the right health care provider.

